##### Follow-up

Six months after the completion of the treatment, follow-up will be performed by telephone to ask if the participants were pregnant.

### Adverse events/serious adverse events

We will monitor adverse events for each treatment during the trial, including hematomas and acute pain. Any adverse events or reactions that are thought to be causally associated with the intervention will be recorded, managed, and reported to the study coordinators. Serious adverse reactions will be reported to the ethical committee.

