### Sample size, randomization, and blinding

Due to the lack of sufficient preliminary studies, it is difficult to determine adequate sample size. According to the studies [23, 24], we hypothesize that the pregnancy rate after MA is 76% and the pregnancy rate after SA is 40%. The calculation equation we used was α = 0.05, 1-β = 0.80 and we determined that a sample size of 36 patients in each group would be sufficient to detect the statistical difference between the two groups, allowing for a 20% withdrawal rate. We will plan to enroll a total of 86 participants with 43 participants in each group. According to the random number sequence generated by Excel, the patients will be randomly divided into either the MA group or the SA group in a 1:1 ratio. We set the blind code in the case for remaining blind when the patients have the adverse effects. The random code and blind code will be conducted by a “third party” independent of the study using opaque envelopes. The envelopes will be sealed and shuffled and the assignment records will not be disclosed until the end of the study. Trial participants, formula doctor, outcome assessors, and data analysts will be blinded to the treatment allocation to minimize potential sources of bias. Because of the special nature of acupuncture, only acupuncturists will not be blinded to the treatment allocation.

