### Outcome measures

Outcomes will be collected at baseline, each menstruation, after three menstrual cycles of treatment, and follow-up at six months after the completion of the treatment. The overview of the outcome measurement at the different time points is shown in Table 3.

**Table 3 Tab3:** Overview of study visits

	Screening and baseline visit	Menstrual cycles			Six months after the last acupuncture treatment
		1st	2nd	3rd	
General condition ^a^	√				
Gynecological examination	√				
Fasting blood samples for sex hormone ^b^, FINS, FBG, HbA1c	√			√	
Transvaginal ultrasound	√	√	√	√	
Pregnancy test (blood β-HCG)				√	
Treatment record ^c^		√	√	√	
Questionnaire ^d^	√			√	
Telephone follow-up ^e^					√

^a^General condition include age, BMI, menstrual and obstetrical histories

^b^Sex hormones include: E2, T, P, FSH, LH, PRL, DHEAS, SHBG

^c^Treatment record includes date and adverse events

^d^Questionnaire includes the PCOS and TCM syndrome scores

^e^Inquires if the participants were pregnant

*E2* estradiol, *T* total testosterone, *P* progesterone, *FSH* follicle-stimulating hormone, *LH* luteinizing hormone, *PRL* prolactin, *DHEAS* dehydroepiandrosterone sulfate, *SHBG* sex hormone-binding globulin, *BMI* body mass index, *FINS* fasting insulin, *FBG* fasting blood-glucose, *HbA1c* glycated hemoglobin

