#### Primary outcome

The primary outcome is the pregnancy rate during the trial, including ectopic pregnancy. Blood β-HCG will be measured at 14 days after ovulation.

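### The adverse event rule records events only when they are thought to be caused by the intervention, names no blinded judge of causality, and conflicts with unfiltered wording elsewhere in the protocol article

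*Protocol article*

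**What the plan says.** Four places in the protocol article bear on this point.

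- **Adverse events/serious adverse events.** The section opens with general monitoring: "We will monitor adverse events for each treatment during the trial, including hematomas and acute pain". Its second sentence sets the recording rule: "Any adverse events or reactions that are thought to be causally associated with the intervention will be recorded"; the same sentence applies this condition to management and to reporting to the coordinators. Its third covers the ethics committee: "Serious adverse reactions will be reported to the ethical committee". The section does not say who judges causality.
- **Outcome measures, Table 3.** Footnote c reads "Treatment record includes date and adverse events", with no causality condition. The treatment record is ticked for the three treatment cycles.
- **Sample size, randomization, and blinding.** "Trial participants, formula doctor, outcome assessors, and data analysts will be blinded to the treatment allocation", and "only acupuncturists will not be blinded to the treatment allocation". The Sham acupuncture group section adds that the sham needle is blunt and does not enter the skin.
- **Primary outcome.** "The primary outcome is the pregnancy rate during the trial, including ectopic pregnancy". No section lists ectopic pregnancy as an adverse event.

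**The concern.** A causality judgement placed before recording acts as a filter. An event judged unrelated need not be written down, so nobody can reassess it later or count it by arm. The usual order is the reverse: record everything, then rate causality. That order lets the rating be checked and lets all events be compared regardless of attribution.

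The filter matters more here because the arms differ visibly in how plausible a needling harm is. Anyone who knows the arm has a reason to see pain or bruising as related after real needling and as unrelated after a blunt, non-penetrating sham. The article does not prevent such a person from making the judgement.

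The same condition returns for serious events. The section heading speaks of serious adverse events, but only serious reactions are to reach the ethics committee.

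Ectopic pregnancy is a harm to the woman that raises the primary success rate. Unless it is also reported as an adverse event, a reader of the results could see it only as a treatment success.

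**Working it through.** The documents give no adverse event rate, harm hypothesis or ectopic rate, so there is no stated figure to reproduce. The check is mainly a comparison of the texts.

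**1. Is the filter stated?** Yes. In the second sentence of the adverse events section, the causality condition governs recording, management and reporting to the coordinators alike.

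**2. Is it consistent with the rest?** No. The first sentence of the same section monitors adverse events without the condition, and footnote c of Table 3 places adverse events in the treatment record without it. An investigator could follow either version.

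**3. Is the judgement protected by blinding?** Not in the text. Participants, the formula doctor, outcome assessors and analysts are blinded; acupuncturists are not. No sentence gives the causality judgement, or completion of the treatment record, to any of these roles.

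**4. What follows arithmetically?** Let t be the true proportion of women with an event and a the probability that an event is judged causal.

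- Recorded proportion in an arm = t × a.
- Lost in an arm = t × (1 − a).
- Spurious difference when t is the same in both arms = t × (a_MA − a_SA).

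The following inputs are assumptions, not protocol content: t from 10% to 30%, a_MA = 80%.

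| a_SA | Spurious difference |
|---|---|
| 80% | 0 |
| 60% | 0.10 × 0.20 = 2 points to 0.30 × 0.20 = 6 points |
| 40% | 0.10 × 0.40 = 4 points to 0.30 × 0.40 = 12 points |

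In the first row, 0.10 × 0.20 = 2 points to 0.30 × 0.20 = 6 points are still lost in each arm. Swapping the two attribution rates reverses the sign. So incomplete capture follows whenever a is below 1, whereas bias needs a to differ by arm. The documents say nothing about a.

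**5. Ectopic pregnancy.** The sample size section plans 43 women per group and hypothesizes pregnancy rates of 76% and 40%, that is 43 × 0.76 = 32.7 and 43 × 0.40 = 17.2 pregnancies, 49.9 in all. Assume that 1% to 3% of pregnancies are ectopic (not from the documents).

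- Expected with manual acupuncture: 32.7 × 0.01 = 0.3 to 32.7 × 0.03 = 1.0.
- Expected with sham: 17.2 × 0.01 = 0.2 to 17.2 × 0.03 = 0.5.
- Chance of at least one in the trial: 1 − 0.99^49.9 = 39% to 1 − 0.97^49.9 = 78%.

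The effect on the pregnancy comparison is small. The issue is how such a case is classified.

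**The case against.** The strongest reply is that the article does not say that unrelated events go unrecorded. It monitors adverse events at each treatment and gives them a place in the treatment record, both without a filter. The second sentence could be loose wording for which events are managed and escalated. This stands in part: it shows that the text is inconsistent, but it does not remove the sentence, which states a rule. For the same reason the point is not merely about detail left to a full protocol.

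A reader might infer several stronger claims that the documents do not support:

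- **That unblinded staff apply the filter.** No section says who judges causality or completes the treatment record. Participants, who would report symptoms such as pain, are blinded, and so is the formula doctor, who adjusts the herbs weekly according to symptoms.
- **That the harm comparison is biased.** Bias needs attribution that differs by arm, which is possible but not shown. The article describes no harm hypothesis or specific between-arm safety test. Its remarks on fewer side effects set acupuncture against ovulation-inducing drugs, which are not an arm of this trial.
- **That ectopic pregnancy is treated only as a success.** Counting it in the primary outcome does not bar reporting it as an adverse event as well.
- **That miscarriage, multiple pregnancy or other pregnancy outcomes are not captured.** This would rest on one-line descriptions of the six-month call in a condensed article. Silence there is not evidence of omission.

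**Conclusion.** The point holds in a limited form. The stated recording rule depends on a causality judgement with no named blinded judge, the ethics reporting rule covers only serious reactions, and both sit beside unfiltered wording in the same article. Followed as written, capture of harms is incomplete in both arms and potentially biased. The potential arises because the acupuncturists know the allocation and only one arm is penetrated.

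The size and direction of any bias cannot be determined from the documents. The differences worked out above come entirely from assumed attribution rates and vanish when those are equal. Ectopic pregnancy is counted in the favourable primary outcome and nowhere named as a harm, so under the filter it could appear only as a success. Few cases are expected, and the primary comparison is little affected. The weakness lies in the harm reporting and should be corrected.

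**What to change.** Reconcile the adverse events section with its own first sentence and with footnote c of Table 3:

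1. Delete the causality condition from the recording rule, so that all adverse events in both arms are recorded.
2. Rate causality afterwards in a separate field, by a role that the article already blinds, such as an outcome assessor. Some events, such as a visible hematoma, may themselves hint at the arm; this is another reason to keep the record and the rating apart.
3. Report serious adverse events to the ethics committee, not only those judged to be reactions.
4. Show ectopic pregnancies separately from the pregnancy rate, and list them also as adverse events.

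Recruitment began in December 2017, so the trial report should say which recording rule was applied to events that have already occurred.

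The cost is a few sentences of protocol wording, one case-report field and one extra line in the results. The downside is more minor events to log.

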### Data analysis

All statistical analyses of the data will be performed using SPSS program V.21.0 (SPSS Inc., Chicago, IL, USA). A *P* value < 0.05 will be considered statistically significant. For cases in which we do not finish all the treatment, we select intention-to-treat (ITT) analysis to avoid the effects of crossover and drop-out. Measured data will be expressed as mean ± SD ($$ \overline{x} $$ ±s) if it obeys a normal distribution or approximate normal distribution. Median (interquartile range [IQR]) will be used if the data do not obey the normal distribution and count data will be expressed in terms of the number of cases. We will use chi-square tests for categorical data and two-sample t-test or Wilcoxon rank sum test for continuous data, according to whether the data are normally distributed. The variance analysis will be performed for the difference between the two groups and within the group. The stratified analysis will be performed to control the confounding factor if necessary. Data analysis will be conducted by statisticians who are independent of the research team.

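### The primary pregnancy analysis is an unadjusted chi-square with an open-ended option to stratify; one pre-specified adjusted model would close that choice and may gain some precision

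*Protocol article*

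**What the plan says.** All references are to the protocol article.

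- Primary outcome: "The primary outcome is the pregnancy rate during the trial", a yes/no outcome for each woman.
- Data analysis: "We will use chi-square tests for categorical data", with significance defined as a P "value < 0.05 will be considered statistically significant". No other test is assigned to pregnancy.
- Data analysis, later in the same paragraph: a stratified analysis may be used to deal with confounding where that proves needed. The text does not name the factors, say what would trigger the analysis, or say which result would then be primary.
- Sample size, randomization, and blinding: "the patients will be randomly divided into either the MA group or the SA group in a 1:1 ratio", from an Excel-generated number list. No stratification factor or minimisation is described. Data analysts are to be blinded.
- Outcome measures, Table 3 footnote a: "General condition include age, BMI, menstrual and obstetrical histories". These are recorded at the screening and baseline visit, before treatment.

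**The concern.** Eligible women are 20 to 40 years old. The Background describes PCOS as diagnosed on two of three findings, so some women may enter with regular cycles and others with amenorrhoea. Age, BMI and cycle status could plausibly affect conception over three cycles. They are already on the case record, yet the stated primary test does not use them.

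Two things are at stake. The first is precision: with 43 women per arm, baseline differences that arise by chance add noise to the pregnancy difference, and a model could remove part of it. The second is pre-specification. An unadjusted test together with an undefined option to stratify allows several defensible P values for one primary outcome, and nothing in the text fixes which one is reported.

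**Working it through.** **Inputs from the protocol article.** Pregnancy 76% (MA) and 40% (SA); "α = 0.05, 1-β = 0.80"; 36 per group before and 43 per group after a 20% withdrawal allowance. Sidedness is not stated; two-sided is assumed.

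**1. The plan's own sample size.** Let p̄ = (0.76 + 0.40)/2 = 0.58.

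n = [1.96·√(2·0.58·0.42) + 0.842·√(0.76·0.24 + 0.40·0.60)]² / 0.36² = (1.368 + 0.547)² / 0.1296 ≈ 28.3, so 29 per group. With continuity correction this becomes 34, against the stated 36. Then 34/0.80 = 42.5, so 43 per group and 86 in total, which matches the plan. (36 × 1.2 = 43.2 also leads to 43; 36/0.80 would give 45.)

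**2. Power of the planned test.** The uncorrected chi-square at 76% against 40% has about 94% power with 43 per arm and 88.8% with 36.

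**3. How often chance imbalance occurs.** The SD of a standardised baseline difference is √(2/43) = 0.216. P(|d| > 0.3) = 2·[1 − Φ(0.3/0.216)] = 16% for one covariate. For at least one of three independent covariates it is 1 − (1 − 0.164)³ = 42%.

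**4. How far such an imbalance moves the result.** Take d = 0.3 on a composite score, split evenly as ±0.15 between the arms. To first order the difference in proportions shifts by at most about ln(OR per SD) × 0.15 × (0.76·0.24 + 0.40·0.60).

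- ln OR 0.3 (OR 1.35): 0.3 × 0.15 × 0.4224 = 0.019, about 2 points.
- ln OR 0.8 (OR 2.2): 0.8 × 0.15 × 0.4224 = 0.051, about 5 points.

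For comparison, the standard error of the unadjusted difference is √(0.4224/43) = 0.099, about 10 points.

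**5. What adjustment would buy.** The article gives no association between these covariates and pregnancy, so a range was assumed. Each setting has 4,000 simulated trials with 43 per arm and all outcomes observed. The chi-square is compared with the likelihood-ratio test from a logistic model with three covariates.

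| Assumed OR per SD of composite | Power, 76% v 40%: chi-square → adjusted | Power, 65% v 40%: chi-square → adjusted | Type I error: chi-square / adjusted | Variance ratio, unadjusted ÷ standardised risk difference |
|---|---|---|---|---|
| 1.0 | 93.7% → 92.9% | 64.9% → 66.7% | 5.7% / 6.1% | 0.96-0.97 |
| 1.35 | 94.1% → 93.9% | 64.3% → 66.9% | 5.9% / 6.2% | 0.98-1.00 |
| 1.65 | 93.3% → 94.0% | 63.6% → 67.4% | 5.5% / 6.3% | 1.01-1.03 |
| 2.2 | 94.0% → 96.0% | 63.8% → 72.0% | 5.4% / 5.5% | 1.09-1.13 |
| 3.3 | 94.3% → 97.6% | 63.6% → 75.2% | 5.2% / 5.2% | 1.21-1.27 |

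In the first row the covariates carry no information and the variance ratio is below 1, so the roughly 2-point rise at 65% against 40% is not a real gain; it goes with the slightly liberal likelihood-ratio test. From OR 2.2 upward the type I errors nearly agree, and the gain is one of precision.

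**The case against.** Much of the opposing case is right, and it limits what can be claimed.

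- **Adjustment is not absent.** A reader who stops at the chi-square sentence might infer that the baseline variables are simply ignored. The later provision for stratified analysis rules that out. What remains is that the provision is optional and undefined.
- **The chi-square is valid.** A reader might infer that chance imbalance biases or invalidates the result. It does not: randomisation already allows for it, and simulated type I error was 5.2% to 5.9%. The loss is in precision and in the estimate given the imbalance that occurred.
- **The power is not free.** The article gives no covariate-outcome association, and 65% against 40% is not an effect it states. At its own planned effect there is little left to gain, and uninformative covariates cost 3-4% in variance.
- **Covariate lists often sit in an analysis plan that is not shown.** This is fair as to missing detail. But the article does assign a test to the primary outcome and then attaches an open condition to it, and that stated text can be improved. Blinding the analysts lessens the risk of a result-driven choice without removing it.
- **No stratification is described, which is not the same as none being used.** This stands; the point does not depend on it.
- **Cycle status may vary little.** If nearly all women enter with oligomenorrhoea or amenorrhoea, that covariate adds little. The article does not give the distribution.

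On the other side, a true difference below 36 points is plausible. The article concedes that preliminary studies are insufficient, and its Background cites a randomised trial that did not support acupuncture for infertility in these women.

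**Conclusion.** The point holds as an improvement in pre-specification and, probably, in efficiency. It is not an error that undermines the trial. The firm part needs no assumption: the primary outcome has an unadjusted test plus an adjustment option with no named factor, trigger or ranking of results.

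The precision part is conditional on assumed odds ratios of 1.0 to 3.3 per SD of a composite, a two-sided 5% test, and 43 women per arm with outcomes. It becomes material only if the covariates are strongly prognostic (about OR 2.2 or more per SD) and the true effect is smaller than planned.

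**What to change.** Before unblinding, replace the open stratification clause, for the primary outcome, with one statement. It should say that pregnancy will be analysed in all randomised women by a logistic model on arm, age, BMI and oligo/amenorrhoea at entry (yes/no), reported as a standardised risk difference with 95% CI. State in the same place how the P value is obtained, because the likelihood-ratio test ran slightly above 5% at this sample size. Say also what is done if a covariate turns out nearly constant. Keep the chi-square as a supportive analysis.

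The cost is a sentence or two and no new data: age, BMI and menstrual history are already collected, and the inclusion criteria already define oligomenorrhoea and amenorrhoea. There are two small downsides. The variance rises by about 3-4% if the covariates prove uninformative. An adjusted odds ratio is not directly comparable with a raw one, which reporting the standardised risk difference avoids. If allocation has already been disclosed, the adjusted model should be labelled as specified afterwards.

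### Continuous secondary outcomes are compared without baseline as a covariate and are also tested within each group; ANCOVA on the collected baseline is more precise, and within-group results should be descriptive only

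*Protocol article*

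**What the plan says.** The Data analysis section of the protocol article names a "two-sample t-test or Wilcoxon rank sum test for continuous data, according to whether the data are normally distributed". It then adds: "The variance analysis will be performed for the difference between the two groups and within the group". On covariates it says only: "The stratified analysis will be performed to control the confounding factor if necessary". The significance rule is that a P "value < 0.05 will be considered statistically significant".

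The baseline data exist. Table 3 under Outcome measures places the fasting bloods and the questionnaire (PCOS and TCM scores) at baseline and again at the third cycle. The sections on syndrome scores and on sex hormones and IRI confirm measurement before and after treatment. Under Interventions, both arms receive the herbal treatment for three cycles. The primary outcome, pregnancy rate, is binary and falls under the chi-square test.

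**The concern.** Two of the stated choices can be improved without collecting anything new.

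- **Precision.** A woman's baseline hormone level or score usually predicts her later one. A between-group comparison that does not condition on baseline leaves that predictable variation in the error term. The trial enrols 86 women and is sized for pregnancy, so the continuous secondary outcomes have little precision to spare.
- **Within-group tests.** A before-after change in one arm mixes the effect of needling with the herbs, time and regression to the mean. Here change is to be expected in both arms. A significant change in one arm and a non-significant change in the other is not evidence of a difference between the arms, but it is easily read as such.

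**Working it through.** **The plan's own figure.** The article gives "α = 0.05, 1-β = 0.80" and states that "a sample size of 36 patients in each group would be sufficient", for pregnancy rates of 76% v 40%. A two-sided two-proportion calculation with continuity correction gives 34 per group (29 without the correction), so 36 is close to reproduced. It concerns the binary primary outcome and does not bear on this point. It is used below only as the plan's number per arm after withdrawals; 43 is the number enrolled per arm. There is no stated precision or power for any continuous outcome to reproduce.

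**Inputs that the article does not give (assumptions).** The baseline-to-post correlation r is taken as 0.3, 0.5 and 0.7. The SD is taken as equal at both times and in both arms, and tests as two-sided at 0.05. The formulas are large-sample and apply to the t-test, not exactly to the rank test.

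**Step 1: relative variance of the between-group difference.** With the post-value test set to 1, a change score has variance 2(1 − r) and ANCOVA has 1 − r². A group-by-time test from an ANOVA with two time points is equivalent to the change-score test. ANCOVA against change is therefore (1 − r²)/[2(1 − r)] = (1 + r)/2.

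| r | Post value | Change score | ANCOVA | ANCOVA ÷ post | ANCOVA ÷ change |
|---|---|---|---|---|---|
| 0.3 | 1 | 1.40 | 0.91 | 0.91 | 0.65 |
| 0.5 | 1 | 1.00 | 0.75 | 0.75 | 0.75 |
| 0.7 | 1 | 0.60 | 0.51 | 0.51 | 0.85 |

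Both ratios are below 1 for every r between 0 and 1. In sample-size terms, the post-value test would need 1/0.91 = 1.1, 1/0.75 = 1.3 or 1/0.51 = 2.0 times as many women to match ANCOVA. At r = 0 there is no gain over the post value.

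**Step 2: what this means at 36 per arm.** The detectable difference at 80% power is (1.96 + 0.84) × √(2/36) = 0.66 SD for the post-value test. Multiplying by √(1 − r²) gives 0.63, 0.57 and 0.47 SD for ANCOVA. Multiplying by √[2(1 − r)] gives 0.78, 0.66 and 0.51 SD for the change score. Power for a true 0.5 SD difference is 56% with the post value and 60%, 69% and 84% with ANCOVA.

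**Step 3: within-group tests when the arms do not differ.** Let both arms have the same true change, d, in units of the SD of change. If p is the power of a paired t-test in one arm, the chance that exactly one arm is significant is 2p(1 − p).

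| n per arm | d | p | 2p(1 − p) |
|---|---|---|---|
| 36 | 0.3 | 0.417 | 49% |
| 36 | 0.5 | 0.831 | 28% |
| 43 | 0.3 | 0.485 | 50% |
| 43 | 0.5 | 0.893 | 19% |

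In half of these discordant trials the significant arm would be MA.

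**The case against.** Several stronger readings are tempting, and the article does not support them.

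- **Baseline is ignored altogether.** This is only one reading. The variance analysis within the group may be a repeated-measures ANOVA, which uses baseline. The precision point survives because it is shown for both readings. Which quantity is tested is a detail that an article may leave to the analysis plan.
- **Choosing the test by normality inflates false positives.** Applied strictly, it does not. In a simulation with 36 per arm and 10,000 runs, the error rate was 4.95% for normal data and 5.1% and 4.7% for two lognormal cases.
- **Efficacy will be claimed from within-group P values.** Nothing says so. The stated comparison is MA v SA, the data analysts are to be blinded and the statisticians independent. The plan permits the misreading but does not commit to it.
- **The conditional stratified analysis will drive the primary result.** No factor or trigger is named, but that is largely detail that an article may omit. The chi-square test is valid under randomisation without adjustment.

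Two cautions about the figures stand. The article names no paired test, so Step 3 illustrates one plausible form. Post-treatment bloods are also tied to the third day of menstruation, so women who conceive during treatment may have none. As an extreme, if all the pregnancies assumed for the sample size occurred then, about 43 × 0.24 = 10 and 43 × 0.60 = 26 women would have post values. The figures in Step 3 would then become about 36% and 58%. ANCOVA does not repair that gap.

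**Conclusion.** The point holds in a limited form, for the continuous secondary outcomes only. The stated analyses are less precise than ANCOVA on either reading of the text. ANCOVA saves 9% to 49% of the variance against the post-value test and 35% to 15% against the change-score test, for assumed r from 0.3 to 0.7. The direction holds for any r between 0 and 1; the size rests on a correlation that the article does not report and on equal SDs.

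Within-group tests do not answer the trial's question and, with no difference between the arms, would often disagree: about 49% to 28% of trials at 36 per arm, under an assumed common change of 0.3 to 0.5 SD. Neither the primary pregnancy comparison nor the sample size is affected.

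**What to change.** 1. Analyse each continuous outcome by ANCOVA of the post-treatment value on arm and its own baseline, with post-treatment and baseline values log-transformed for skewed hormones and HOMA-IR. Report the adjusted difference (a ratio on the log scale) with its 95% CI.
2. Report within-group changes descriptively, without P values.
3. Keep the chi-square comparison as the single primary analysis of pregnancy. Label any stratified or covariate-adjusted analysis as supportive, with its factors fixed before unblinding. Age and BMI are already recorded: "General condition include age, BMI, menstrual and obstetrical histories".
4. State how women without a post-treatment value are handled, including those who conceive before the final blood sample.

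The cost is analysis wording. No visit, measurement or treatment changes, and SPSS fits the model. Item 4 needs some thought, but the planned tests face the same gap.
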